#### **6.1.6. Visit 6: Follow-up Visit on Day 28 Post Delivery (Window: Day 28 to Day 42)**

The subject will have the following procedures performed at this visit at ANC:

- Concomitant treatment history;
- Limited physical examination;
- Vital signs;
- Hemoglobin level (with HemoCueTM);
- A nasopharyngeal swab for macrolide resistant and penicillin resistant *Streptococcus pneumoniae* from subjects who were tested at baseline;
- AE assessments;

- General physical exam of neonate;
- Outcome research/resource utilization data collection.

#### **6.1.7. Follow-up Visit at About 6 Months after Last IPTp Course (in a Limited Number of Subjects Only)**

- Concomitant treatment history;
- Limited physical examination;
- Vital signs;
- A nasopharyngeal swab for macrolide resistant and penicillin resistant *Streptococcus pneumoniae* from subjects who were tested at baseline.
- AE assessments.

#### **6.1.8. Unscheduled Visit**

In the event that subjects require an unscheduled visit (eg, for additional follow up due to any safety concerns, concomitant illness etc), the following assessments/procedures should be completed at a minimum:

- Symptom-directed physical exam with vital signs;
- Assessment of fetal viability or neonatal examination;
- AE assessments;
- Concomitant treatment history.

Subjects and/or their babies who develop clinical symptoms of malaria (fever  $>37.5^{\circ}\text{C}$ , oral), or any other illness at any time during study period will be asked to report to the study physician immediately for further evaluation. **Any additional tests, procedures, treatments, and consultations may be conducted if recommended by local/national ANC guidelines.**

#### **6.2. Subject Withdrawal**

Subjects may withdraw from the study at any time at their own request, or they may be withdrawn at any time at the discretion of the investigator or sponsor for safety, behavioral, or administrative reasons. If a subject does not return for a scheduled visit, every effort should be made to contact the subject. In any circumstance, every effort should be made to document subject outcome, if possible. The investigator should inquire about the reason for withdrawal, request the subject to return all unused investigational product(s), request the subject to return for a final visit, if applicable, and follow-up with the subject regarding any unresolved adverse events.

If the subject withdraws from the study and also withdraws consent for disclosure of future information, no further evaluations should be performed and no additional data should be collected. The sponsor may retain and continue to use any data collected before such withdrawal of consent.

**Unless subject withdraws the consent or leaves the town/village, she should continue in the study for follow-ups until Day 28 (window 28 to Day 42) post delivery.** Subject may be **withdrawn from study treatment** due to safety concerns (eg, adverse events, significant laboratory abnormalities, contraindications of concomitant medications), but not from the clinical study per se. Subject will receive standard ANC care as per local ANC guideline. If a subject is withdrawn from the AZCQ IPTp regimen, she will be switched to the standard IPTp regimen as per local guidelines and will undergo regular follow up visits. If she receives an SP IPTp course during the study, she will be subsequently followed up as per follow up schedule for subjects receiving SP IPTp regimen. The circumstances and data surrounding conditions of withdrawal should be clearly documented in the case report form. The investigator must record the primary reason for discontinuation. A discontinuation must be reported immediately to the Pfizer medical monitor or his/her designated representative if it is due to an SAE.

## 7. ASSESSMENTS

All study related assessment will be performed after obtaining informed consent. Every effort should be made to ensure that the protocol required tests and procedures are completed as described. Field workers will be engaged at each site to maximize the dosing compliance and to minimize loss to follow-up visits. However it is anticipated that from time to time there may be circumstances, outside of the control of the investigator that may make it unfeasible to perform the test. In these cases the investigator will take all steps necessary to ensure the safety and well being of the subject. When a protocol required test can not be performed the investigator will document the reason for this and any corrective and preventive actions which he/she has taken to ensure that normal processes are adhered to as soon as possible. The study team will be informed of these incidents in a timely fashion.

The followings are key study assessments. The completed data collection and guidance are provided in CRF and its completion guideline. The detailed descriptions of the procedures (ie, sampling, handling, testing, storage, and shipment of the biological samples) and whether materials (ie test tubes and labels) will be supplied by Pfizer will be provided in a separate document as a lab manual.

### 7.1. Safety Assessments:

Safety and tolerability will be assessed by spontaneously reported adverse events, vital signs, physical examination, safety laboratory tests including hemoglobin and urine test for glucose and protein, and adverse pregnancy outcomes for mothers and by the general physical examination for the neonates through Day 28 (window: Day 28 to Day 42) post delivery.

- Adverse events assessments: refer to Section 8 (Adverse Event Reporting);

- Complete physical exam (including general appearance, throat, neck, thyroid, musculoskeletal, skin, lymph nodes, extremities, pulses, pulmonary, cardiac, abdominal, and neurological examination) at baseline or limited physical exam (including general appearance, brief pulmonary, cardiac, abdominal and neurological examination or symptom directed exams) at Visit 5, 6, and 7 from the activity schedule;
- Vital signs: include weight, sitting blood pressure, pulse rate and oral temperature;
- Routine obstetric checkup: include fetal height, fetal heart beat, fetal position;
- Obstetrical ultrasound: will be performed on Day 0 of Visit 1 only if urine pregnancy test is positive. The assessments include current gestational age (weeks), congenital abnormality, or any malformation.
- Laboratory tests:
  - Urine pregnancy test: will be performed if not done at any prior ANC visit for this pregnancy;
  - Hemoglobin levels: with HemoCue™, via finger stick or peripheral blood collection;
  - Urine analysis for glucose & proteins.
- Pregnancy outcomes: refer to Section 7.2 for details;
- General physical examination of the neonate at birth (within 2 days for home delivery) and at Day 28 (Day 28 - Day 42): weight, length, head circumference, APGAR scores (1/5 minutes at birth only), Ballard scores, congenital anomalies, clinical/hospital visits/stays, and other complications, etc;
- Concomitant treatment assessments.

## 7.2. Efficacy Assessments

- Adverse pregnancy outcomes: defined as live-borne neonate (singleton) with LBW (<2,500g), premature births (<37 weeks), abortion (≤28 weeks), still birth (>28 weeks), lost to follow-up prior to termination of pregnancy or delivery, or missing birth weight of the neonates. Following are some details:
  - LBW: defines as birth weight less than 2500 g (up to and including 2499g);
  - Abortion: defines as a pregnancy loss before 28 completed weeks of gestation (≤28 weeks);

- Stillbirth: birth of a baby showing no signs of life. It defines as a pregnancy loss after 28 weeks of gestation (>28 weeks);
- Premature births: the neonate born prior to 37 weeks of gestation (<37 weeks);
- Lost to follow-up prior to termination of pregnancy or delivery.

The sites are asked to make every attempt to follow up subjects through Day 28 post delivery unless the consent is withdrawn.

- Neonate outcomes at birth: birth weight, length, APGAR scores (1/5 minutes), Ballard scores, congenital abnormalities, perinatal and neonatal deaths, ophthalmia neonatorum (lab diagnosis):
  - Birth weight: The weight of a neonate determined immediately after delivery or as soon as feasible thereafter. If home delivery, the subject should contact the study site as soon as possible when the delivery occurs. Field workers will visit home as early as possible within 2 days of subject reporting delivery. Digital weight scale will be used for accurate readings;
  - Ophthalmia neonatorum: laboratory diagnosis will be performed among neonates with purulent discharge. A sample of conjunctival exudates will be taken on a sterile cotton swab before the treatment is given. The collected sample will be sent to a central lab to test *N. gonorrhoeae* and *C. trachomatis* using PCR assay (Amplicor CT/NG, Roche). The standard presumptive treatment/prophylaxis for ophthalmia neonatorum will be given to neonates at birth per local treatment guidelines;
- Hemoglobin levels: HemoCueTM, via finger stick or peripheral blood collection;
- Diagnosis of pre-eclampsia from Week 20 to delivery:
  - (1) Systolic blood pressure of at least 140 mmHg and/or diastolic blood pressure of at least 90 mmHg, measured on two separate readings taken at least 4 hours apart, AND
  - (2) Proteinuria at least 300 mg protein in a 24 hour urine collection.
- Peripheral blood smears at Week 36 - 38 of gestation and at birth from subjects with hospital delivery: Thick and thin peripheral blood smears prepared using standard Giemsa staining method for parasite identification and count if positive. The blood smears will be read in a blinded fashion (blinded to study treatment and the reading of other microscopists);

- Placental blood smear: will be prepared from placental blood at birth from subjects who deliver at hospital. Thick and thin blood smears (2 smears per subject) will be prepared using standard Giemsa staining method for parasite identification and count. The blood smears will be read by at least two microscopists in a blinded fashion (blinded to study treatment and the reading of other microscopists);
- Placental histology: a sample of placenta tissue (size: about 2cm x 2cm x 1cm) will be collected at birth from the subjects who deliver at hospital for histological examination when feasible. Refer to lab manual for details;
- Cord blood smear: will be prepared from cord blood at birth from subjects with hospital delivery. Thick and thin blood smears (2 smears per subject) will be prepared using standard Giemsa staining method for parasite identification and count. The blood smears will be read by at least two microscopists in a blinded fashion (blinded to study treatment and the reading of other microscopists).
- Sexually Transmitted Infections (STIs)/Reproductive Tract Infections (RTIs) laboratory tests:

A. *T. pallidum* test:

- At Baseline: *T. pallidum* screening test: this will be a blood screening test using Rapid Plasma Reagin (RPR) method. It is often normally conducted at the first ANC visit. If the result is available, it will be transcribed to study case report form. If it is not done at previous ANC check up, the *T. pallidum* screen test will be conducted in consistent with local/national ANC guideline. The test result is not required at the enrollment.
  - At Weeks 36 -38 of gestation: blood samples (~0.5 ml) will be collected and serum will be used for the tests:
    - Rapid Plasma Reagin (RPR): a non-treponemal specific serological screening test. Positive test indicates a high likelihood of *T. pallidum* infection, although not necessarily current, active disease;
    - Treponema Pallidum Particil Agglutination Assay (TPPA): a confirmatory test when RPR is positive. This is a treponemal test for the serologic detection of antibodies to the various species including *T. pallidum*. The test is used to confirm the reactive results of a non-treponemal screening test for *T. pallidum* or as a diagnostic test in patients with a nonreactive nontreponemal test but with signs or symptoms suggestive of late syphilis.
- B. *N. gonorrhoeae* and *C. trachomatis* test at Weeks 36 - 38 of gestation: an endocervical swab will be collected and PCR assay (Amplicor CT/NG, Roche) will be used for analysis;

- C. Bacterial vaginosis at Weeks 36 - 38 of gestation: a vaginal swab will be collected for Gram staining;
- D. *Trichomonas vaginalis* at Weeks 36 - 38 of gestation: a vaginal swab will be collected for the lab test. Refer to lab manual for details.
- Clinical presentations/diagnosis at any time during the study period through Day 28 post delivery. This information will be recorded on related CRF pages.
  - Clinical episode of malaria: subjects presenting with clinical symptoms of malaria (fever  $>37.5^{\circ}\text{C}$ , oral) and diagnosed (either by rapid diagnostic tests or microscopy) with malaria;
  - Sexual Transmitted Disease (STIs): include *T. pallidum*, *N. gonorrhoeae*, *C. trachomatis*;
  - Bacterial infections including pneumonia and other lower respiratory tract infections.
- Subjects requiring additional treatments for malaria during the study period following the first dose (diagnosed based on clinical presentation and/or lab test results);
- *P.f.* genetic resistance marker tests at Weeks 36 - 38 of gestation: A dried blood blot will be collected from all subjects but tests will be done only from subjects with parasitemia. Polymerase Chain Reaction (PCR) assay will be used and following markers will be tested:
  - CQ resistance markers in AZCQ treatment group: Pfcrt/Pfmdr1;
  - SP resistance markers in SP treatment group: pfdhfr/ pfdhps.
- Macrolide and Penicillin resistance tests for *Strep. pneumoniae*:
  - Nasopharyngeal swabs will be collected from approximately 600 subjects each in AZCQ and SP arms from at least 2 sites at three time points: (1) at baseline (Visit 1), (2) at Day 28 - Day 42 post delivery (Visit 6), and (3) at about 6 months post last IPTp course (Visit 7). This is to test *Streptococcus pneumoniae* sensitivity against three antibiotics: azithromycin, erythromycin and penicillin. Refer to lab manual for details.

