| Hemoglobin (Hb)                                                              | X                               |                    |                    | X                               |                    |                    | X                               |                    |                    | X                        | X t           | X                                 |                                          |
| Urine Pregnancy Test j                                            | X                               |                    |                    |                                 |                    |                    |                                 |                    |                    |                          |                          |                                   |                                          |
| Urine tests for glucose & protein                                            | X                               |                    |                    | X                               |                    |                    | X                               |                    |                    | X                        |                          |                                   |                                          |
| Randomize Subjects                                                    | X                               |                    |                    |                                 |                    |                    |                                 |                    |                    |                          |                          |                                   |                                          |
| Administer Treatment                                                  |                                 |                    |                    |                                 |                    |                    |                                 |                    |                    |                          |                          |                                   |                                          |

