#### Other Secondary Efficacy Endpoints

1. Hemoglobin concentrations at 36-38 weeks of gestation;
2. Occurrence at birth of a neonate with congenital abnormalities;
3. Occurrence of a perinatal or neonatal deaths;
4. Birth weight of the live-borne neonate (singleton);
5. Number of episodes of symptomatic malaria per subject anytime from first IPTp dose administration to delivery;
6. Occurrence of a subject requiring additional treatment for malaria during the study period following the first dose (diagnosed based on clinical presentation and/or lab test results);
7. Occurrence of peripheral parasitemia at 36-38 weeks of gestation;
8. Occurrence of peripheral parasitemia at delivery;
9. Occurrence of cord blood parasitemia at delivery;
10. Occurrence of STIs including *T. pallidum*, *N. gonorrhoeae*, *C. trachomatis* during the study period following first dose (diagnosed based on clinical presentation prior to Week 36-38 and/or lab test results between Week 36-38);
11. Occurrence of a positive result for *C. trachomatis* infection at 36-38 weeks of gestation (diagnosed based on lab result);
12. Occurrence of a positive result for *N. gonorrhoeae* infection at 36-38 weeks of gestation (diagnosed based on lab result);
13. Occurrence of a positive result for *T. pallidum* test at 36-38 weeks of gestation (diagnosed based on lab result);
14. Occurrence of a *T. vaginalis* infection at 36-38 weeks of gestation (diagnosed based on lab result);

15. Occurrence of bacterial vaginosis at 36-38 weeks of gestation (diagnosed based on lab result);
16. Occurrence of ophthalmia neonatorum (diagnosed based on lab test results) in the neonate;
17. Occurrence of bacterial infections including pneumonia and other lower respiratory tract infections anytime from first IPTp dose administration to delivery;
18. Occurrence of pre-eclampsia from Week 20 to delivery;
19. Occurrence of nasopharyngeal swabs positive for macrolide resistant and penicillin resistant *Streptococcus pneumoniae* at baseline, at Day 28 (window Day 28 - Day 42) post delivery, and at about 6 months following last IPTp course. This test will be done in about 600 subjects each from the AZCQ and SP arms from two or more sites.

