#### **4.2. Exclusion Criteria**

Subjects presenting with any of the following will not be randomized in the study:

1. Age <16 years old or >35 years old.
2. Multiple gestations (more than one fetus) as per the ultrasound results at screening.
3. Clinical symptoms of malaria.
4. Hemoglobin < 8 g/dL (measured at baseline).
5. Any condition requiring hospitalization or evidence of severe concomitant infection at time of presentation.
6. Use of antimalarial drugs in previous 4 weeks.
7. History of convulsions, hypertension, diabetes or any other chronic illness that may adversely affect fetal growth and viability.
8. Inability to tolerate oral treatment in tablet form.
9. Known allergy to the study drugs (AZ, CQ, and SP) or to any macrolides or sulphonamides.
10. Present history of smoking or alcohol or drug abuse since first becoming aware of current pregnancy.
11. Participation in other studies within 30 days before the current study begins and/or during study participation.
12. Inability to comprehend and/or unwillingness to follow the study protocol.
13. Concurrent participation in another investigational study.
14. Previously randomized in this study.
15. Requirement to use medication during the study that might interfere with the evaluation of the study drug (eg, trimethoprim-sulfamethoxazole use in subjects positive for HIV infection) or is contra-indicated during pregnancy per package inserts.

16. Severe acute or chronic medical or psychiatric condition or laboratory abnormality that may increase the risk associated with study participation or investigational product administration or may interfere with the interpretation of study results and, in the judgment of the investigator, would make the subject inappropriate for entry into this study. Examples would include but not limited to:
  - a. Symptomatic HIV infection, including physical findings that suggest immunocompromised status (eg, oral candidiasis);
  - b. Neurological conditions which may predispose to complications during pregnancy, including seizure disorders;
  - c. Severe psychosis or major disorder that may interfere with the conduct of the study or adherence to study medication;
  - d. Known, clinically significant pre-existing renal or hepatic disease.
17. Evidence of current obstetric complications that may adversely impact the pregnancy and/or fetal outcomes, including presence of congenital anomalies, placenta previa or abruption.

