### 9.2.1. Analysis of Primary Endpoint

The primary efficacy endpoint of the trial is the presence of subjects with a sub-optimal pregnancy outcome defined as any of the following: live-borne neonate (singleton) with low birth-weight (or LBW for short, defined as live birth weight <2,500g), premature births (<37 weeks), abortion (≤28 weeks), still birth (>28 weeks), lost to follow-up prior to termination of pregnancy or delivery, or missing birth weight of the neonate. The primary analysis set will be the ITT, and will exclude multiple gestations. Secondary analyses will also be repeated using the per protocol analysis set.

Percentage of subjects with sub-optimal pregnancy outcome will be estimated for each treatment group. The following descriptive statistics will be available:

- Sample size (n) per group;
- Number of subjects with sub-optimal pregnancy outcome (m);
- Proportion of subjects with sub-optimal pregnancy outcome:

$$\hat{p} = \frac{m}{n}$$

- Two sided CI will be formed for the proportion of subjects using the normal approximation to the binomial:

$$\hat{p} \pm z_{1-\alpha/2} \sqrt{\frac{\hat{p}(1-\hat{p})}{n}}$$

The final results will be expressed in percentages, ie, proportions x 100. If the lower confidence limit is <0, it will be set to 0. If the upper confidence limit is >100%, it will be set to 100%.

The Mantel-Haenszel estimate of the common risk ratio will be computed using SAS Proc Freq, adjusted for the randomization strata. The risk ratio will be the proportion of AZCQ subjects with sub-optimal pregnancy outcome over the proportion of SP subjects with sub-optimal pregnancy outcome. The estimated variance for  $\ln(RR_{MH})$  given by Greenland and Robins will be utilized. The two-sided p-value will be calculated using the Wald test statistic on the natural log risk ratio scale.

Additional analysis models for the primary endpoint will be used to examine the interaction of a range of effects with treatment group. These effects include randomization strata, HIV status at baseline, age, and country. An alpha level of 0.05 2-sided will be used for these additional analyses.

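### The 24-hour urine criterion for pre-eclampsia cannot be met from the scheduled data, and the planned HIV interaction has no named source for HIV status

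*Protocol*

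**What the plan says.** **Pre-eclampsia.** Section 2.2 of the Protocol lists as other secondary endpoint 18: "Occurrence of pre-eclampsia from Week 20 to delivery". Section 7.2 gives the diagnosis in two parts. The first is a blood-pressure threshold, "measured on two separate readings taken at least 4 hours apart, AND". The second, joined to it by that conjunction, is "Proteinuria at least 300 mg protein in a 24 hour urine collection".

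The urine row in the Schedule of Activities reads "Urine tests for glucose & protein" and is marked at Visits 1 to 4 only. Section 7.1 describes the test simply as "Urine analysis for glucose & proteins". Blood pressure comes with the vital signs: "Vital signs: include weight, sitting blood pressure, pulse rate and oral temperature". Vital signs are marked at every visit, including delivery.

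**HIV.** Section 9.2.1 plans additional models of the primary endpoint that examine interactions with treatment: "These effects include randomization strata, HIV status at baseline, age, and country". In subject selection, HIV appears only inside examples. Exclusion criterion 15 mentions "trimethoprim-sulfamethoxazole use in subjects positive for HIV infection", and criterion 16a gives symptomatic infection as an example of an excluding condition.

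**The concern.** An endpoint definition is only as good as the data collected to apply it. Here the definition demands a quantitative timed collection, and the scheduled procedures contain a simple urine test. If the protocol is followed exactly, nobody can be classified as a case. Any cases would come from work-up that a site orders on its own initiative.

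The protocol itself gives this endpoint a rationale: Sections 1.4.2.3 and the Protocol Summary suggest that chloroquine may protect against pre-eclampsia. A comparison meant to examine that idea would partly reflect which sites order 24-hour collections and for whom. The trial is open label, and Section 5.2 blinds only laboratory staff and microscopists, so the decision to order a collection is made with the treatment known.

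For HIV, a planned interaction needs a baseline value for each woman. Without a named source, the analysis would rest on whatever happened to be written down. The protocol does not say whether a woman without an entry counts as negative or as unknown. Neither gap can be fully repaired after enrolment: an analysis plan can say how missing values are handled, but it cannot supply a measurement that was not taken.

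**Working it through.** No sample size, power or alpha figure is at issue, so the check sets what each analysis needs against what is collected.

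1. **24-hour urine collection.** It is required by Section 7.2. It is absent from the Schedule of Activities and from the visit lists in Sections 6.1.1 to 6.1.4, which contain only the glucose and protein test. No rule converts a positive test or a raised blood pressure into a timed collection.

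2. **Urine at delivery.** The endpoint window runs to delivery. Neither the hospital list (6.1.5.1) nor the home list (6.1.5.2) contains a urine test, so the last scheduled test is at Visit 4, Weeks 36 to 38.

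3. **Coverage from Week 20.** Visit 1 falls at Weeks 14 to 26. With 4 to 8 weeks between courses:
   - Visit 2 falls between 14 + 4 = 18 and 26 + 8 = 34 weeks.
   - Visit 3 falls no earlier than 18 + 4 = 22 weeks, and by rule should be no later than Week 36.
   - A woman enrolled at Week 14 with 4-week gaps has tests at Weeks 14, 18, 22 and 36 to 38, so two lie inside the window.
   - A woman enrolled at Week 26 has all four inside it.

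   Even the simple test therefore covers the window unevenly, depending on gestation at entry.

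4. **Blood pressure.** It is taken at every visit. Section 7.2 sets a minimum of 4 hours between the two readings and no maximum, so readings at successive visits satisfy the wording. This part can be met from scheduled data.

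5. **What the conjunction does.** A woman whose pressure is never raised is a non-case whatever her urine shows. A woman with two raised readings and no collection cannot be classified. Section 9.2 treats subjects lacking the data needed for an endpoint as missing, so read literally the missing values fall on the women who may be cases.

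6. **How the protocol handles other conditional tests.** It writes the trigger: conjunctival sampling if there is purulent discharge, the confirmatory syphilis assay if the screening test is positive, resistance markers if the smear is positive. Pre-eclampsia has no such line. It is also missing from the list in Section 7.2 of clinical diagnoses recorded at any time (malaria, STIs, bacterial infections).

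7. **HIV status at baseline.** It is required by Section 9.2.1. No HIV test or status item appears in the Schedule of Activities, in the Visit 1 procedures or in Section 7. Section 6 allows earlier antenatal results to be transcribed, but for tests the protocol requires, and HIV is not among them. By contrast, syphilis has a schedule row, a footnote and an explicit transcription rule.

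**The case against.** The strongest reply is that pre-eclampsia is an event-driven diagnosis and its work-up need not be a scheduled procedure. Rapid tests for clinical malaria are not in the schedule either. Screening is scheduled (blood pressure, urine protein and an obstetric checkup at Visits 1 to 4), Section 6.1.8 permits further tests where local guidelines recommend them, and Section 8.4 foresees abnormal results that need more diagnostic work.

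Part of this stands: some cases would be confirmed in ordinary care. But the malaria work-up has a written trigger, fever above a stated threshold, while pre-eclampsia has none. Section 6.1.8 gives permission; it does not ensure ascertainment.

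On HIV, Visit 1 takes a medical history and a treatment history, the exclusion criteria make the investigator think about HIV, and Section 7 refers the full data list to a case report form that is not shown. That also stands. A reader might infer that HIV status is recorded nowhere, and the documents do not support this. They show only that the protocol names no source. History would in any case capture known and disclosed status only.

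A reader might also infer that the repeat blood-pressure reading is never collected. That fails too, because successive visits supply readings at least 4 hours apart.

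**Conclusion.** The point holds in a limited form. The proteinuria criterion cannot be satisfied from scheduled data, so endpoint 18 would be ascertained only through discretionary local work-up. The baseline HIV interaction has no specified data source. Both conclusions rest on the protocol text alone; a form field could weaken the second, but no form field produces a 24-hour collection.

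The size is modest. Pre-eclampsia is one of 19 other secondary endpoints, and HIV status is one of four effects listed for additional interaction models. The primary endpoint and its analysis, the one-sided alpha of 0.000625, the sample size range of 2,602 to 5,044 and the stopping rules are untouched.

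Two further inferences should be resisted. The loss of power for pre-eclampsia cannot be calculated, because the documents give no incidence, no expected effect and no proportion of women who would be worked up; any figure would simply reflect the assumptions chosen. Bias between arms is possible but not shown. The design gives AZCQ women two home visits per course and SP women one (6 against 3 over three courses), so contact differs. Those home visits list no blood pressure or urine test, and the documents do not show whether work-up would differ or in which direction.

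**What to change.** **Pre-eclampsia.** Reconcile Section 7.2 with the Schedule of Activities and Sections 6.1.1 to 6.1.5, so that the data named in the definition are those collected from Week 20 to delivery, by the same rule in both arms. Either the schedule states when the required urine measurement is taken or triggered, or the definition is matched to the measurements already scheduled. Which diagnostic criterion to use is for the sponsor's clinicians. Whichever is chosen, the text should cover the delivery visit and say how a woman with raised blood pressure but no confirmatory urine result is classified.

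**HIV.** Add to Section 6.1.1 and the case report form a single item, HIV status transcribed from the antenatal record where available, with an explicit unknown category. Otherwise delete HIV status from Section 9.2.1.

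**Cost.** Matching the definition to the scheduled measurements costs wording and one form field; adding or triggering a timed collection would also add a procedure at sites. Some women will still have unknown HIV status, so the interaction would apply to those with a recorded result. The changes should be made before enrolment, since neither item can be fully recovered later.
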